### Phase 1 Study: Baseline Data Collection (9 Months)

#### Overview

Phase 1 will be conducted as follows: (1) Prior to the introduction of the study to wider NU clinical staff members, staff knowledge, experiences, and opinions about the role of fathers and FICare will be assessed by a questionnaire. (2) Once a parent is recruited, the PSS:NICU [26] and MH questionnaires (GAD-7 [27] and PHQ-9 [28]) will be given to complete within 7 days. (3) Fathers or partners will be invited to participate in 2 semistructured interviews, within 2 weeks of recruitment and immediately prior to discharge. The interviews will explore their MH, experiences of bonding with baby, understanding the neonatal environment, and reflecting on their service expectations. Based on the father’s or partner’s preference, interviews will be undertaken either in a private room on the NU or digitally via MS Teams at a mutually convenient time. Interviews will be digitally recorded and are anticipated to last up to 1 hour. Data saturation is expected at around 12-15 fathers. (4) The parents will be asked to complete the PSS:NICU, GAD-7, and PHQ-9 questionnaires at 3 weekly intervals, finishing on the week of discharge, to monitor their MH through their NU stay. (5) Up to 4 groups of 5 mothers will be invited to participate in a focus group to assess their wellbeing, experience of the NU, and their perspective on support for and from their partners. This will occur in a room in the NU at a time convenient to the mothers. Groups will be organized until data saturation is reached. (6) Telephone interviews and emailed questionnaires will be completed by parents at 4-6 weeks postdischarge to assess family confidence and bonding after NU discharge.

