### Washout Period, Phase 2 Preparation (4 Months)

A program to enhance father participation with the FICare model will be developed using the existing Neonatal DadPad or Imperial Family Delivered Neonatal Care app. Both of these apps are currently used in several NHS Trusts to guide fathers through their NU journey. The phase 1 and systematic review findings, along with guidance from the PAG will inform our decision for what is best suited for our local population.

Teaching sessions will be undertaken to educate and upskill all clinical NU staff on the study aims, recruitment, phase 1 study findings, and upcoming phase 2 study, highlighting the importance of fathers’ role in the FICare (eg, teaching parents how to safely give nasogastric feeds and nappy changes in a ventilated baby). In addition, there will be regular FICare teaching for staff, including encouragement of parents to attend ward rounds, and with guidance to parents in the workbook (Table 2).

**Table 2 table2:** Program to enhance father involvement in family integrated care.

Strategies	When	Who
Educational booklet or app, including Introduction to the neonatal unit Meeting the multidisciplinary team—tailored to the individual unit Family integrated care Taking care of yourselves Routine care and “observations” Breastfeeding Developmental care Medications Nutrition and growth Ventilation and breathing support Cardiac (heart) conditions Gastrointestinal and liver (gut) conditions Brain development Planning for discharge Eyes	At parents’ disposal	Both parents
Suggested tasks or workbook, including Kangaroo care Nappy changes in incubator Mouth care and cleaning of baby Reading of observations (heart rate, temperature, respiratory rate) Helping to weigh baby Bathing baby Ward round participation	To work through at parents’ pace	Both parents
Peer support sessions—led by specialist clinical psychologists or therapists	Every two weeks	Fathers^a,b^
Ward round participation	Daily	Both parents^a^
Bite-size education classes	2-3 per week at varying times including weekend	Both parents^a,b^

^a^Any parent in the unit is welcome to participate or attend.

^b^Sessions to occur at times to suit fathers with cultural, religious, family, and work obligations, as determined through phase 1 data collection.

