### Phase 2 Study: Enhanced Father Involvement in FICare (9 Months)

Once a family is recruited, the program developed to enhance the father’s involvement in FICare will be implemented to take place at the parents’ pace (Table 2). Materials will be freely available to the study participants in a format suited to their needs (electronic or paper copy). All interested parents are encouraged to attend the peer support sessions, ward round participation, and bite-size education classes.

The NU experience and MH status of both parents will be assessed as in the phase 1 study (Figure 1) including assessing their experience of the FICare program. At the end of the phase 2 study, staff knowledge, experiences, and opinions about fathers and FICare will be reassessed and compared with the start of the study.

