### Questionnaires

For descriptive statistics, the median and mode scores of the PSS:NICU, GAD-7, and PHQ-9 will be used to describe the outcome of the questionnaires. For inference analysis, the difference in median for the PSS:NICU, GAD-7, and PHQ-9 at admission, discharge, and 6 weeks postdischarge will be compared between phase 1 and phase 2 using the Mann-Whitney test and the paired 2-tailed *t* test. The data will be checked for outliers and these will be corrected or removed. However, where these outliers are accurate, a nonparametric statistical analysis will be performed. Depending on the data type, missing data will be replaced with mean, median, or mode. In addition, regression and multiple imputations analysis will also be used to impute or generate missing values.

Staff survey questionnaire responses to individual questions will be presented as a percentage of individuals responding yes or no. The percentage of “yes” responses to each question by the staff at the start and end of the study will be compared by paired *t* test.

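### The staff survey's yes/no answers are to be compared by a paired t test, which suits neither the percentages nor binary answers; no linkage of individual staff is described (minor)

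*Protocol article*

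**What the plan says.** Under Phase 1 Study, Overview, before the study is introduced to the wider unit staff, "staff knowledge, experiences, and opinions about the role of fathers and FICare will be assessed by a questionnaire". Under Phase 2 Study, at the end of that phase, "staff knowledge, experiences, and opinions about fathers and FICare will be reassessed and compared with the start of the study".

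The analysis is in Methods, Questionnaires. On presentation: "Staff survey questionnaire responses to individual questions will be presented as a percentage of individuals responding yes or no". On the comparison, a paired *t* test is named for the share of 'yes' at the two surveys: "responses to each question by the staff at the start and end of the study will be compared by paired" …

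The section headings give planned durations of 9 months for phase 1, 4 months for the washout and 9 months for phase 2. The article does not say whether the same individuals complete both surveys, whether the forms carry an identifier, or how many staff or questions there are.

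**The concern.** A paired *t* test needs several paired, roughly continuous differences. What is described is a yes/no answer, summarised as one percentage per question per survey. The sentence does not settle what a pair is: a question's two percentages, the set of questions, or a staff member's two answers. None of these makes the paired *t* test the natural choice, and they fail in different ways.

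At stake is the only test the article plans for change in staff knowledge and opinion. The Discussion calls raising staff skills and awareness a focus of the methods, so the result is likely to be reported. No parent outcome depends on it.

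**Working it through.** The article gives no sample size, expected percentage or significance level for the staff survey, so there is no stated figure to reproduce. From the documents come the binary answers, the named test and the gap of 9 + 4 + 9 = 22 months. Staff numbers, question counts, 'yes' rates and correlations below are assumptions.

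The statistic is t = d̄ / (s_d/√m) with m − 1 degrees of freedom, where m is the number of pairs.

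**1. Each question's two percentages as the pair.** Here m = 1, so there are 0 degrees of freedom and s_d is undefined. Entering 60% and 75% returns no p value.

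**2. Questions as the pairs.** This runs on the reported percentages. Take Q questions, n different staff at each survey, a common 'yes' rate p, and correlation r between two answers of one person.
- True variance of the mean difference: (2/n) p(1−p) [1 + (Q−1)r]/Q.
- Variance the test estimates, on average: (2/n) p(1−p) (1−r)/Q.
- Ratio: [1 + (Q−1)r]/(1−r). This exceeds 1 whenever r > 0, and n cancels, so surveying more staff does not cure it.

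Simulated type I error with no true change, 15 questions and 60 different staff per survey (two separate runs):

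| Latent within-person correlation | Type I error (nominal 5%) |
|---|---|
| 0 | 5.4%; 5.4% |
| 0.1 | 13.4%; 14.5% |
| 0.2 | 22.3%; 23.9% |
| 0.3 | 28.0%; 30.7% |

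**3. Linked staff as the pairs.** Let b staff change from no to yes and c from yes to no, among n. Then d̄ = (b−c)/n and s_d² = [(b+c) − (b−c)²/n]/(n−1). For 60% to 75% with n = 100, b = 25 and c = 10:
- d̄ = 15/100 = 0.15.
- s_d² = (35 − 2.25)/99 = 0.331, so s_d = 0.575.
- t = 0.15/0.0575 = 2.61, p = 0.0105. Exact McNemar gives 0.0167.

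The same two percentages with other discordant counts:

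| b, c | Paired *t* p | Exact McNemar p |
|---|---|---|
| 15, 0 | 0.00006 | 0.00006 |
| 20, 5 | 0.0023 | 0.0041 |
| 25, 10 | 0.0105 | 0.0167 |
| 40, 25 | 0.062 | 0.082 |

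The unpaired chi-square gives 0.024. The two percentages alone therefore do not fix a paired result; the linkage does.

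Simulated type I error of the paired *t* test on linked answers (20,000 runs per setting; within-person correlation 0 or 0.5) was 0.035 to 0.054 at 'yes' rates of 50% to 80% and n = 20 to 100. At 95% 'yes' and n = 20 it was 0.001 to 0.011, and the differences had zero variance in 14% to 38% of runs.

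**4. Staff paired without a true link.** With unequal numbers of respondents, say 60 and 48, pairs cannot be formed. With equal numbers and different people, type I error was about 0.04 to 0.05 (0.011 at 95% 'yes' and n = 20). If the same people answer but the link is lost, it fell below 0.01. Power for 50% to 70% with n = 50 and correlation 0.5 then dropped from 0.71 to 0.55.

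**The case against.** The best defence is that the plan intends linked forms. The words 'reassessed' and 'paired' are compatible with that, and form coding is a detail an article may leave to the full protocol. For linked answers at moderate 'yes' rates the paired *t* test is close to nominal and tracks McNemar's test. Where it fails, near the ceiling with few staff, it errs on the conservative side, and exact McNemar is conservative there too (0.0004 or less at 95% 'yes' and n = 20).

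Much of this stands, and it rules out three stronger readings that a reader might infer:
- *That the staff are unlinked.* The article is silent. It supports only the statement that no linkage is described. That turnover over 22 months would break many pairs is inference; no staff numbers or turnover are given.
- *That a paired t test is always invalid for binary answers.* The figures for linked staff do not bear this out. It is a poor choice there, not a wrong one throughout.
- *That the planned test has a type I error of 13% to 31%.* Those figures belong to the questions-as-pairs reading with assumed inputs. The sentence speaks of each question, which more naturally means one comparison per question.

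What the defence does not rescue is the stated method. It is described as a comparison of percentages, and on those it is either not computable or dependent on the number and correlation of the questions.

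**Conclusion.** The point holds as a poorly specified analysis of the staff survey. As worded, per question and on percentages, the paired *t* test has no degrees of freedom. With questions as pairs, type I error rises with any positive within-person correlation; its size rests on assumed question counts and correlations. With linked staff it is an adequate approximation at moderate 'yes' rates and a weak one with few staff near 100%. With unlinked staff its main costs are lost power and pairs that cannot be formed.

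Severity is minor. The staff survey is not among the article's numbered objectives or its primary and secondary outcomes, and the study is sized on qualitative saturation. A reader might treat this as a defect that threatens the trial's conclusions; the Objectives and Outcomes sections do not support that.

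**What to change.** Replace the paired *t* test in Methods, Questionnaires, and state whether individual staff responses are linked.

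- **If linked:** for staff who answered both surveys, use McNemar's exact test per question, with the paired difference in proportions and its 95% CI. The gain is a p value that is always defined and error control that does not rest on an approximation; it is not extra power.
- **If not linked:** compare the two proportions per question by Fisher's exact or a chi-square test, with the difference and its 95% CI. State that staff who answer both times make the samples overlap, which typically makes the test conservative. With the same staff at both surveys and correlation 0.5, the simulated chi-square type I error was 0.001 to 0.008.
- **In both cases:** report how many staff answered at each survey and, if linked, how many answered both.

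The cost is a change of wording. The start survey was planned before the study was introduced to staff, and 22 families had been recruited by October 2023, so it has probably been done. If those forms carry no identifier, one cannot be added now and the unlinked analysis is the one available.

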### Data Storage and Availability

All patient-identifiable data will be stored in a locked office of the principal investigator (PI) of participating sites. Access to identifiable data will be restricted to the PI and research team. The paper questionnaires will be stored securely in a file kept in the locked research office and electronic versions will be stored in a password-protected NHS computer. The electronic version of questionnaires will be emailed by parents to a secure NHS email account. This will also be used if transcription or audio files need to be transferred with third-party transcription services. Third-party services will be vetted as per NHS standards to ensure data protection and confidentiality. The sponsor will have access to the pseudoanonymized data if requested. Anonymized data will be made available on request. Study data will be kept for up to 18 months after the study completion.

### Potential Risk to Participants and Mitigation

Considering the nature of the study, it is unlikely to have any adverse events. However, fathers may feel the additional burden of fulfilling their expected NU obligations alongside their breadwinner role and feelings of guilt for being unable to fulfill the expectations set for them [30,31]. To mitigate this difficulty, there is flexibility in when and to what extent fathers would like to be involved in FICare set at their own pace. The questionnaires and interviews may be emotionally challenging. This is being mitigated by the option to attend peer support sessions run by an appropriately trained professional and all parents will have access to the local neonatal psychologist. Interview frameworks were reviewed by the PAG and neonatal psychologist. A protocol is in place for any participants exhibiting severe MH symptoms through questionnaire responses or other forms of communication. Adverse events will be reported to the chief investigator and local research and development office and follow research and development, protocols with consideration of modification of study procedures if required.

Adverse events in the hospital setting will follow local hospital protocols as well as escalation to study PI with consideration of modification of study procedures if required. The risk of psychological distress resulting from study participation has been minimized with the support of a specialist psychotherapist who reviewed the study design and materials. A protocol is in place for any parents exhibiting severe MH symptoms through questionnaire responses or other forms of communication. We do not anticipate any risks to parents as they are simply being encouraged to participate in standard FICare activities that already occur in the participating centers. There is an emphasis that this should occur at the parents’ pace.

### Dissemination

The study findings will be presented at neonatal and FICare conferences and published in medical and nursing journals. The study findings will also be shared with relevant charities (eg, Bliss), and the study participants if they wish. It will form the basis of a PhD thesis. The PAG will be involved in the dissemination of the study findings.

### Ethical Considerations

Participants will be able to withdraw from the study at any point. Anonymized data gathered until this point will be retained for data analysis. Following each interview or focus group, parents will be given 2 weeks to withdraw their data from the study. The study was approved by Leicester, South Research Ethics Committee (22/EM/0140)in August 2022, and written consent will be obtained from participants (see participant information leaflets and consent forms in Multimedia Appendices 1 and 2).

## Results

The study is currently ongoing. As of October 2023, 22 families, comprising 22 fathers and 17 mothers had been recruited. The SR studies have been registered with the PROSPERO database (324275 and 306760). The projected end date for data collection is around July 2024, data analysis will occur in November 2024, and publication of the study findings will occur in early 2025.

## Discussion

This study will test the hypothesis that if fathers are facilitated to engage more with their baby on the NU and are better supported during the neonatal stay, both parents will experience fewer MH symptoms during their baby’s hospitalization and up to 6 weeks postdischarge. Improving parents’ MH is shown to allow greater parent-child bonding [32] and more sensitive responsiveness of mothers to their infants’ cues [33]. Mothers engaged in the FICare model have greater confidence in caregiving at the point of discharge and seek less medical support after discharge [32]. It is anticipated that these results will translate to fathers or partners.

Unlike many other studies [12,33], this study includes parents of a wide gestational age range of premature infants, including extremely premature infants and those who are invasively ventilated and at the highest risk of adverse outcomes. This is vital as research has found that fathers find the fragile appearance of their premature infants causes significant stress [34]. A focus of the study methods will be to upskill NU staff to increase awareness and understand the importance of father engagement in FICare and their MH as well as the impact on mother and child, which is in line with the NHS Long Term Plan [17].

Limitations of the study include the need for conversational English. This is required to be able to complete the standardized questionnaires, participate in the interviews and focus groups, and to be able to engage with the phase 2 provisions. The language for the phase 2 materials will be kept as simple to ensure readability and understanding. Exclusion from recruitment based on language will be monitored. The perceived research burden may disproportionately impact parents who have older children, have a greater distance to travel, limited parental leave, or who do not have English as their first language. There may also be cultural barriers to overcome when discussing MH.

A prospective cohort study was the most practical and ethical study design. The sample size and the primary outcome of the study is based on the qualitative data. A bigger sample size will be required for the study to be based on the quantitative or questionnaire data. The quantitative or questionnaire data collected in this study is to support the qualitative data and to test the feasibility of collecting such data longitudinally.

The PSS:NICU questionnaire has been translated into many languages across the world [35,36], and is a well-used tool in neonatal research. It has been validated in mothers and fathers of NICU babies in the United Kingdom [37]. There are limited validated tools to assess paternal and maternal anxiety and depression in the postpartum or NU period. Therefore, simple screening tools that are validated in primary care and the general population for patients with a variety of backgrounds and stages of life were chosen [27,38,39].

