**Objective:**

The primary aim of this study is to investigate the impact of supporting father or partner engagement in FICare of preterm infants on their MH up to 6 weeks postdischarge. The secondary aim is to investigate the impact on maternal MH.

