## Introduction

In 2019, in England and Wales, 49,489 premature births were recorded, and the majority would have required a neonatal unit (NU) admission [1]. Scientific and technological advancements have led to significant reductions in mortality and morbidity for preterm infants [2], and now the importance of decreasing psychosocial morbidity for the family unit is being addressed. Admission of a critically ill baby to the NU is a deeply traumatic time for parents and may result in parental mental health (MH) difficulties during and after discharge [3,4]. Studies exploring paternal experiences in the NU highlight fathers feeling neglected and in a unique position of stress, trying to balance work and home life to allow the mother to focus on their sick baby [5]. As paternal and maternal MH are closely linked, supporting the fathers could also positively impact maternal MH [6,7]. A recent study has shown reduced paternal stress in relation to the provision of family integrated care (FICare) in single-family rooms, but it only included parents of babies who did not require intensive care [8].

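### The phase comparison in mothers can describe the whole enhanced FICare package, but not the effect on mothers of supporting fathers

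*Protocol article*

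**What the plan says.** **The exposure.** The Abstract (Objective) sets the primary aim as to "investigate the impact of supporting father or partner engagement in FICare of preterm infants on their MH". It then adds: "The secondary aim is to investigate the impact on maternal MH". Read together, the two sentences make support of the father the exposure for both parents.

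**The route to mothers.** The Introduction explains why mothers should benefit: "As paternal and maternal MH are closely linked, supporting the fathers could also positively impact maternal MH". The Discussion turns this into a hypothesis to be tested. The cause is that "if fathers are facilitated to engage more with their baby on the NU and are better supported during the neonatal stay"; the result is that "both parents will experience fewer MH symptoms during their baby’s hospitalization and up to 6 weeks postdischarge".

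**The programme.** Table 2 (in the section on the washout period and phase 2 preparation) lists five strategies with a column for who receives them. The booklet or app, the tasks or workbook, ward round participation and the education classes are for both parents. Peer support is listed for fathers. Footnote a, attached to peer support, ward rounds and classes, reads: "Any parent in the unit is welcome to participate or attend". The Phase 2 section agrees: "All interested parents are encouraged to attend the peer support sessions, ward round participation, and bite-size education classes".

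**The comparison.** Under Questionnaires, the PSS:NICU, GAD-7 and PHQ-9 scores are compared between phase 1 and phase 2. Outcomes lists maternal stress, parental anxiety and parental depression as secondary. It also lists the father's engagement with FICare, but not the mother's.

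**The concern.** The cause named for mothers (their partner is supported) is not the only thing that changes for them between the phases. They are offered most of the programme themselves. The Abstract (Background) and the Introduction both say that FICare improves maternal MH, so on the article's own account a direct effect on mothers is to be expected.

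If maternal scores are lower in phase 2, the stated aim and hypothesis invite the reader to credit the support given to fathers. The mother's own use of the booklet, workbook, ward rounds and classes is at least as plausible an explanation. What is at stake is the interpretation of a secondary aim, and any argument for a father-sensitive model that leans on maternal benefit. The limitations in the Discussion do not mention mothers' own access.

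**Working it through.** No sample size, power or error rate is involved. The check is a count and an argument about what the comparison can identify.

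**1. Count of Table 2 by recipient.**

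| Strategy | Listed for | Footnote a (open to any parent) |
|---|---|---|
| Booklet or app | Both parents | no |
| Tasks or workbook | Both parents | no |
| Peer support | Fathers | yes |
| Ward round participation | Both parents | yes |
| Education classes | Both parents | yes |

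Listed for both parents: 4 of 5. Listed for fathers: 1 of 5. Closed to mothers once footnote a is applied: 0 of 5. Ward rounds also appear as a workbook task; counting them once gives 3 of 4 for both parents, and still none closed to mothers.

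**2. What the maternal contrast contains.** Let D be the effect of the mother's own use of the programme, F the effect that reaches her through the supported father, and P any change over time between the phases. In the simplest additive form:

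phase 2 minus phase 1 in mothers = D + F + P

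Even with P = 0, the comparison yields one quantity, D + F. A true state with D = d and F = 0 gives the same expected difference as one with D = 0 and F = d. The data cannot tell them apart.

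**3. Is there any group that separates them?** To isolate F, one would need mothers whose partner was supported while they had no access to the programme themselves, or some equivalent contrast. Phase 1 mothers have neither; phase 2 mothers have both. Recruiting more families would estimate D + F + P more precisely without separating its parts.

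**4. Can D be taken as zero?** No, for two reasons. The article says FICare benefits mothers. And although Study Centers says a FICare culture already exists at both sites, the same section says there is no formal programme. Potential Risk to Participants and Mitigation describes the activities as ones that already take place. This makes D smaller than it would be against no FICare at all. It does not make it zero, because the workbook, educational material and classes are new for mothers as well.

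**The case against.** The case on the other side has real content.

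- **The secondary aim does not ask for an effect split by route.** Taken alone, the sentence asks only for the impact on maternal MH, and objective 4 is framed around introducing the programme. This stands in part: a whole-programme reading is available and can be addressed. But the Introduction and the Discussion hypothesis name support of the father as the cause, so the aim is not left at that reading.
- **The questionnaires are supportive only.** The Discussion says a larger sample would be needed to base the study on them. This lowers the weight of the point. It concerns precision, however, whereas the difficulty here is attribution, and the same section still says the hypothesis for both parents will be tested.
- **Mothers' focus groups cover support for and from partners** (Phase 1, Overview), and phase 2 repeats the assessments. This stands: the father-to-mother route can be explored qualitatively. It does not separate the routes in the questionnaire comparison.
- **Some elements are aimed at fathers**, namely staff teaching on their role and session times chosen to suit them (footnote b). This is true, but they arrive in phase 2 together with the two-parent package.

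A reader might infer more than the article supports:

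- **That the maternal comparison is of no use.** The whole-package effect can still be described, subject to period effects.
- **That four-fifths of any maternal effect is direct.** The row count shows what is offered, not what is used or what it achieves; uptake is at the parents' own pace.
- **That classes offered to mothers can be set against peer sessions for fathers as a measure of dose.** That needs an assumed length of stay, and peer support is not closed to mothers.
- **That the study is bound to report a misattribution.** No reporting rule says so; the wording of the aim and hypothesis only makes it likely.

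**Conclusion.** The point holds as a mismatch between the maternal claim and the programme. All five strategies are open to mothers, four of them by listing and the fifth by footnote. The phase difference in mothers therefore estimates the effect of the whole package plus any period effect, and the effect of supporting fathers is not identifiable within it.

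The conclusion rests on two things stated in the article: the recipients in Table 2 with footnote a, and FICare's own benefit for mothers. It needs no assumption about length of stay or attendance. The relative size of the two routes is unknown and cannot be worked out from the article.

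The weight is moderate: this is a secondary aim in a study sized on qualitative saturation. Correction is still worthwhile, because it changes what the study may conclude about mothers.

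**What to change.** 1. Restate the maternal secondary aim, the maternal half of the Discussion hypothesis and the corresponding conclusion as the effect of the enhanced FICare programme offered to both parents.
2. Add mothers' own access to the programme to the limitations.
3. Do not attribute a change in maternal questionnaire scores to father engagement. Present what the focus groups say about partner support as qualitative exploration of that route.
4. Optionally, where feasible, record each parent's use of the programme separately and report it descriptively as exploratory. The article describes no such records, so they may have to be set up. With at most 20 families per phase and mothers' participation optional (17 mothers from 22 families by October 2023), they should not be presented as separating the two routes.

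**Cost.** Items 1 to 3 are wording and can be settled before the analysis planned for November 2024. They need no extra participants or visits and leave the programme unchanged. Item 4 adds some record keeping. The downside is that the maternal claim becomes less specific to father support.
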